### Statistical analyses

#### Sample size

Sample size was calculated for the primary outcome, HAQ score, and the primary analysis of the non-inferiority design using two-sample *t*-tests and data from the CAMERA-II trial: mean (SD) HAQ score at 18 months 0.38(0.4) [15]. An equivalence margin of 0.2 in HAQ scores between study arms was considered clinically acceptable. A sample size of 51 per group was calculated to obtain a power of 80% at a one-sided *p* value of 0.05. Taking into account 10% drop-out, total sample size was set at 112 patients.

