#### Primary outcome analyses

The primary outcome is HAQ score; the primary analysis is a general linear model, testing HAQ scores at 18 months between the two arms according to intention to treat (ITT), controlling for baseline HAQ, center (stratification factor in the randomization), and the baseline covariates age, gender, disease activity (DAS28), rheumatoid factor, and anti-CCP. The ITT population will include all randomized patients as long as they have taken study medication at least once and at least one efficacy measurement was obtained. Secondary analyses are 1) the primary analysis, but for the per protocol population (i.e., all patients without major protocol violations or a switch between study arms), and 2) a mixed model analysis comparing HAQ scores over time (baseline and 3, 6, 12, and 18 months) between the study arms. In this model we will control for the same covariates as those in the primary analysis. Although this model handles missing data well, if ≥ 10% of data are missing, as a sensitivity analysis data will be analyzed after multiple imputation if data seem to be missing at random.

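### The secondary mixed model uses baseline HAQ as both an outcome time point and a covariate, which distorts the model and, if one arm effect across visits is reported, dilutes it by one fifth

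*Protocol article*

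**What the plan says.** All of this is in the protocol article, section *Primary outcome analyses*, unless noted.

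- The primary analysis is a general linear model of HAQ at 18 months, "controlling for baseline HAQ, center (stratification factor in the randomization), and the baseline covariates age, gender, disease activity (DAS28), rheumatoid factor, and anti-CCP". Baseline HAQ is only a covariate here.
- Two secondary analyses follow. The first is announced as "Secondary analyses are 1) the primary analysis, but for the per protocol population". The second is "a mixed model analysis comparing HAQ scores over time (baseline and 3, 6, 12, and 18 months) between the study arms".
- On the second, the article adds: "In this model we will control for the same covariates as those in the primary analysis".
- *Sample size* sets the margin: "An equivalence margin of 0.2 in HAQ scores between study arms was considered clinically acceptable". It is tied there to the primary analysis.
- *Objectives and primary and secondary outcomes and their rationale* names the course of HAQ change over time as a secondary outcome. The mixed model is the analysis that addresses it.

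The article does not say whether the mixed model has an arm-by-time term, which contrast is read from it, or what its covariance structure is. It does not apply the 0.2 margin to this model.

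**The concern.** Baseline is one of the five response times, and baseline HAQ also enters as a covariate through the cross-reference to the primary analysis. For the baseline row the response is then identical to one of its predictors. The arms cannot differ there once the covariate is in the model, the true slope in that row is 1, and its residual is zero. At follow-up the slope is lower and the residual is not zero. One slope and one residual variance cannot fit both.

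The direction of any dilution matters because the trial seeks to show that HandScan guidance is no worse. An arm difference pulled toward zero favours that conclusion, so a secondary analysis with this fault could appear to confirm the primary result more firmly than the data do.

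**Working it through.** **Inputs from the article (*Sample size*, *Primary outcome analyses*):** margin 0.2; SD of HAQ at 18 months 0.4; one-sided 0.05; power 80%; 51 evaluable per arm; five response times including baseline.

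**Assumed, because the article does not give them:** correlation r between baseline and each follow-up HAQ; correlation ρ between follow-up visits (0.3 to 0.7 for both); baseline SD (0.4 or 0.65); complete data; a true difference of 0.2 at every follow-up visit.

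**1. The plan's own figure.** The exact two-sample t calculation gives power 0.799 at 50 per arm and 0.806 at 51. The stated 51 reproduces.

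**2. Distorted slope.** With equal SDs, the slope on baseline is r at follow-up and 1 in the baseline row. The common slope becomes (1 + 4r)/5. At r = 0.3 this is (1 + 1.2)/5 = 0.44 instead of 0.30. With baseline SD 0.65 and follow-up SD 0.4, the follow-up slope is 0.3 × 0.4/0.65 = 0.185, and the common slope is (1 + 4 × 0.185)/5 = 0.35. An arm-by-time term does not cure this. In the equal-SD case a chance baseline imbalance is over-corrected by 0.44 − 0.30 = 0.14 of its size.

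**3. Dilution with a single arm term.** With five equally weighted visits, the arm effect is (0 + 0.2 + 0.2 + 0.2 + 0.2)/5 = 0.16. Over the four follow-up visits it is 0.20. Simulation with 51 per arm, SD 0.4 and 4,000 runs per setting gave means of 0.159 to 0.160 with the baseline row and 0.198 to 0.200 without it.

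**4. Consequence if that estimate were compared with 0.2.** Given baseline, the mean of four follow-up visits has variance V = 0.16 × [(1 − ρ)/4 + ρ − r²], and SE = √(2V/51). Adding the baseline row multiplies both estimate and SE by 0.8. The probability of falsely declaring non-inferiority is then Φ(0.04/(0.8 SE) − 1.645).

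| r | ρ | V | SE | 0.8 SE | False non-inferiority |
|---|---|---|---|---|---|
| 0.3 | 0.3 | 0.0616 | 0.0491 | 0.0393 | 27% |
| 0.5 | 0.5 | 0.0600 | 0.0485 | 0.0388 | 27% |
| 0.7 | 0.7 | 0.0456 | 0.0423 | 0.0338 | 32% |
| 0.3 | 0.7 | 0.1096 | 0.0656 | 0.0524 | 19% |

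The 4,000-run simulations at r = ρ = 0.3, 0.5 and 0.7 gave 28%, 27% and 32% with the baseline row, against 5% to 6% without it. Fitted random-intercept models (300 runs each) gave 29% and 35% at correlations 0.5 and 0.7, against about 3% without the baseline row. The 35% has a Monte Carlo SE of √(0.35 × 0.65/300) ≈ 2.8 points, so it is compatible with 32%. Runs with a baseline SD of 0.65 and mixed correlations gave 19% to 24%. Hence roughly 20-32%.

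**5. Arm-by-time term, 18-month contrast, baseline still in the response.** Mean estimates were 0.199 and 0.196 at correlations 0.5 and 0.7, so the one-fifth dilution is gone. The mean model SE was 0.0635 against an empirical SD of 0.0705 (ratio 0.90), and 0.0516 against 0.0574 (ratio 0.90). This is the distorted residual variance at work. The false non-inferiority rate was 8% and 6%, with a Monte Carlo SE around 5% of √(0.05 × 0.95/300) ≈ 1.3 points, so any inflation here is small.

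**The case against.** The strongest reply is that the harm in steps 3 and 4 needs two things the article does not state. It fixes no arm effect averaged over visits: comparing scores over time between arms fits an arm-by-time model at least as well. It also attaches no non-inferiority test to the mixed model. Interaction terms and contrasts are commonly left to the analysis plan, and their absence from an article is no fault. This stands. A reader might infer that the plan will produce a diluted estimate and a false non-inferiority claim; the document supports that only conditionally. Nor does it support reading the fault into the trial's main conclusion, which rests on the 18-month general linear model.

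A second reply is that the covariates carried over might mean only the list from age to anti-CCP, leaving baseline HAQ out. The wording allows this, but it is the less natural reading, because baseline HAQ is the first item the primary model controls for. At the least, the text needs to say so.

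A third reply is that the size depends on unstated correlations and SDs. That is true, and it is why a range is given. Every value in the range is well above 5%.

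A reader might also extend the point to the SF36 and EQ5D mixed models. The section *Secondary outcomes* lists baseline among their time points but states no baseline covariate, so no double use is shown there.

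These replies limit the consequence. They do not remove the double use, which is stated text rather than an omission.

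**Conclusion.** The point holds as a specification fault in a secondary analysis. On the plain reading, baseline HAQ is both response and covariate, which distorts the common baseline slope and the residual variance in any version of the model. The one-fifth dilution arises only if a single arm effect across visits is reported, and the figure assumes complete data and compound symmetry. The 20-32% false non-inferiority is conditional further on comparing that estimate with 0.2, and on the assumed correlations and SDs. With arm-by-time read at 18 months, what remains is an over-corrected baseline imbalance and, in the two settings fitted, a model SE about 10% too small. The primary analysis and the sample size are not affected. The text should be corrected, but the fault does not threaten the trial's primary conclusion.

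**What to change.** State one role for baseline HAQ in the mixed model. Either:

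- use HAQ at 3, 6, 12 and 18 months as the responses and keep baseline HAQ as a covariate; or
- keep baseline as a response with a mean constrained to be common to both arms, and remove baseline HAQ from the covariates.

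In either case include an arm-by-time term and name the 18-month arm contrast as the quantity to be reported. The cost is one line of model specification. It needs no new data and changes neither the primary analysis nor the sample size.

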#### Secondary outcomes

Quality of life will be evaluated at baseline and after 3, 6, 12, and 18 months using SF36 and EQ5D questionnaires with mixed model analyses between study arms.

Cost-effectiveness of the HandScan arm versus the DAS arm treatment will be calculated from actual data (i.e., a trial-based economic evaluation). In the HandScan arm, cost for a rheumatologist at the clinical visits will only be included if a rheumatologist would have actually been required, e.g., to change medication. To prevent overestimation of cost of rheumatologist time, a visit rate of once per month during the first 6 months and once per 3 months thereafter will be assumed for cost calculation. Cost-effectiveness planes and acceptability curves will also be estimated from the societal (base case), healthcare, and hospital perspectives. Differences in quality-adjusted life years (QALYs; life years multiplied by the utility value, as calculated using EQ5D) and costs (for drug cost, other direct costs, and indirect costs) will be calculated using bootstrapping (5000 resamplings, with replacement). Costs and QALYs will be discounted by 4% and 1.5% according to the Dutch guidelines for pharmaco-economic evaluations. Sensitivity analyses will be performed for time spent by rheumatologists, number of visits, QALYs (according to either EQ5D or SF36), costing method (Human Capital Approach or Friction costs method), and discount rates. Missing data for costs and QALY calculation will be imputed using multiple imputation.

Radiographic joint space width and bone erosions of hands and feet will be measured by SvdH score, [16] total score, and separately for joint space narrowing and erosion scores. Differences in change at 18 months from baseline between arms will be tested for statistically significant differences with Mann-Whitney U tests, and with generalized linear mixed models. As sensitivity analysis, joint space narrowing scores by a novel [10], fully automated assessment will be performed and analyzed. Moreover, cumulative disease activity according to area under the curve of HandScan data in each arm will be correlated to radiographic damage (total, narrowing, and erosion scores) by SvdH and automated assessments by Spearman correlation analyses.

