### Assessments

Patients will visit the outpatient clinics monthly (Fig. 1). At each visit, disease activity will be measured, to ensure blinding both with HandScan and DAS44, consisting of serum CRP, a 44 joints assessment for swelling and tenderness, and a PGA (VAS 0–10 cm, 10 = worst). At baseline and 3, 6, 12, and 18 months patients will fill out the HAQ (first outcome), the Short Form Health Survey (SF36), EuroQol (EQ5D), and the questionnaire on direct and indirect costs (second outcome). Direct costs (health care) and indirect costs (loss of paid and household productivity) will be calculated from questionnaires, including the Health and Labour questionnaire [13]. Radiographs in the antero-posterior direction of hands, wrists, and feet will be obtained at baseline and 18 months (second outcome). The current gold standard for scoring these radiographs is the Sharp/van der Heijde scoring method [11]. This method scores erosions (score 0–5 per region) and joint space narrowing (score 0–4 per region) of these joints and sums the scores to the SHS score, ranging from 0 to 448. A newly developed fully automated radiographic scoring system of hand and wrist joints is also applied to quantify changes in the joint space width over time.

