### Prevention of under- and overtreatment in the HandScan arm

Since treatment guidance by the HandScan is a novel approach, measures are taken to prevent large deviation of the HandScan-guided strategy from the DAS guided strategy to avoid under- or overtreatment. If treatment decisions dictated by HandScan at three consecutive monthly visits (Fig. 3) are discordant with decisions that would have been dictated by DAS, patients will be switched to the DAS-guided arm and medication decisions will be immediately guided by this arm. Discordancies are tracked in the software application; the switch is implemented without intervention of the researcher, blinded for researcher and patient. This way, patients in the HandScan arm might potentially be under- or overtreated (based on DAS guidance) only for a maximum of two consecutive months.

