## Discussion

This study aims to evaluate clinical efficacy of a HandScan-guided versus DAS-guided tight-control and treat-to-target treatment strategy for early RA. The HandScan guidance has potential drawbacks, mainly because it relies solely on arthritic activity in hands and wrists. However, optical spectral transmission (OST) did correlate to DAS28 in a previous study [6], as well as to US assessed synovial inflammation of hand and wrist joints, while DAS28 did not correlate with these US results. It is possible that, considering the strengths and weaknesses of both guidance methods, the optimal guidance for future treatment of early RA would be using both methods or a combination of parameters of both methods (e.g., HandScan with CRP measurement).

An economic evaluation of guidance of a tight-control strategy using the HandScan has been previously published [17]. Implementation of the HandScan as a monitoring tool was modeled at comparable costs and comparable effects as using clinical assessments. To validate this result, cost-effectiveness in the current study will be calculated based on actual data (i.e., a trial-based economic evaluation); this approach requires less assumptions and therefore has a lower risk of bias.

This protocol describes a specifically designed software application to allow for double-blind, safe, and patient-tailored guidance of treatment. Implementation of the software application has the advantage that it allows for on-site patient randomization and double-blind (for the guidance method) treatment. Deviation from standard treatment schedules is allowed, for example, by defining a MTD or the opportunity to switch from MTX to LEF in case of MTX intolerance. Three consecutive discrepancies in medication advice between the HandScan and DAS arm lead to switch of the respective patients in the HandScan arm to the DAS arm as a built-in safety for potentially large differences between arms. Importantly, as neither the patient nor the physician is aware of a switch, the double-blind design will be maintained.

This specifically designed decision-making software application also allows for implementation of other RCTs testing future, novel methods of guidance of tight-control and treat-to-target treatment strategies in RA.

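### The economic base case pairs effects obtained with HandScan plus a DAS safeguard with rheumatologist costs of HandScan guidance alone

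*Protocol article*

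**What the plan says.** The costing rule is in the protocol article under Secondary outcomes: "In the HandScan arm, cost for a rheumatologist at the clinical visits will only be included if a rheumatologist would have actually been required". A change of medication is given as an example of such a need. No corresponding condition is stated for the DAS arm. The next sentence, meant to avoid overstating specialist time, says that "a visit rate of once per month during the first 6 months and once per 3 months thereafter will be assumed for cost calculation". It does not name an arm.

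The conduct of the trial is described elsewhere. Under Assessments, "Patients will visit the outpatient clinics monthly", and "At each visit, disease activity will be measured, to ensure blinding both with HandScan and DAS44". Under Prevention of under- and overtreatment in the HandScan arm, the safeguard is triggered as follows: "If treatment decisions dictated by HandScan at three consecutive monthly visits" disagree with what DAS would have dictated, then "patients will be switched to the DAS-guided arm and medication decisions will be immediately guided by this arm".

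The same Secondary outcomes section says that cost-effectiveness "will be calculated from actual data (i.e., a trial-based economic evaluation"). The Discussion repeats that "cost-effectiveness in the current study will be calculated based on actual data" and gives this as a reason for a lower risk of bias than an earlier modelled evaluation. Sensitivity analyses are listed for rheumatologist time and number of visits, among other items, without ranges.

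**The concern.** A trial-based economic evaluation should attach costs to the strategy that produced the effects. Here the HandScan arm's quality-adjusted life years come from HandScan guidance backed by a monthly clinical assessment, with DAS guidance taking over when the two disagree persistently. The rheumatologist cost is that of a strategy in which a specialist is called only when needed. The safeguard may improve the arm's effects, yet no stated analysis clearly charges for it.

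The abstract gives greater cost-effectiveness of the HandScan arm as part of what the trial is to investigate. A difference in specialist visits that follows from a costing convention would enter that comparison as if it had been observed. Bootstrapping would not reveal it, because resampling reproduces a systematic rule in every replicate.

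**Working it through.** The protocol states no cost figure to reproduce, so the check counts rheumatologist visits charged per patient.

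**Inputs from the protocol article**
- Duration: 18 months (Methods/design).
- Actual visits: monthly, about 18 after baseline (Assessments).
- Assumed visits for costing: 6 in the first 6 months and 12/3 = 4 thereafter, so 6 + 4 = 10 (Secondary outcomes). 10/18 = 56% of the actual number.

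**Assumption, not in the protocol**
- q is the share of HandScan-arm visits at which a rheumatologist would have been required. Shown at 0.25, 0.50, 0.75 and 1.

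**Formula.** Let V_D and V_H be the visits costed in the DAS and HandScan arms. With every DAS-arm visit charged, the difference in charged visits produced by the rules alone is V_D − q × V_H. Positive values favour HandScan.

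| Reading of the assumed schedule | Formula | q = 0.25 | q = 0.50 | q = 0.75 | q = 1 |
|---|---|---|---|---|---|
| Covers both arms | 10 − 10q | 7.5 | 5.0 | 2.5 | 0 |
| Covers neither (both at 18) | 18 − 18q | 13.5 | 9.0 | 4.5 | 0 |
| Covers the DAS arm only | 10 − 18q | 5.5 | 1.0 | −3.5 | −8 |

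The second row is a reference case, showing what the schedule changes. At q = 0.50, applying the schedule to both arms reduces the rule-driven saving from 9.0 to 5.0 visits. If the schedule covers the DAS arm only, the sign turns at q = 10/18 = 0.56.

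**Visits after a switch.** Let s be the share of costed HandScan-arm visits that fall after transfer to DAS guidance, with q the same before and after. On the common 10-visit schedule:
- costing by randomized arm gives a saving of 10 × (1 − q);
- costing visits after a switch as DAS-arm visits gives 10 × (1 − q) × (1 − s);
- the difference, 10 × (1 − q) × s, is saving credited to patients who are no longer guided by HandScan.

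At q = 0.50, each 0.10 of s accounts for 10 × 0.50 × 0.10 = 0.5 visit. The protocol gives no expected value of s. It does not treat switching as negligible: under Patient safety, inclusion stops only if more than ten switches occur among the first 20 patients with 6 months of data. With 1:1 allocation, about ten of those 20 are in the HandScan arm.

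**Schedule against conduct.** Under Treatment strategy, patients are evaluated monthly throughout, and a flare leads to renewed escalation. After month 6 a patient can therefore need treatment changes more often than the assumed quarterly visits. The protocol does not say which governs the cost then, the need for a rheumatologist or the schedule.

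**One rule for both arms.** If both arms are costed by the same rule and schedule, the difference produced by the rule itself is 0. What remains reflects observed resource use.

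**The case against.** The strongest defence is that lower specialist time is part of what the HandScan is meant to deliver. The Background says an assistant without medical training can operate it. The Assessments section gives blinding as the reason for dual measurement, and leaving out visits made only for the trial is an accepted costing choice. Forcing one rule on both arms removes this rule-driven difference by construction, and charging a full DAS44 to the HandScan arm costs a trial hybrid that nobody would use in practice. This stands, and it is why the rule should remain in the base case for visits under HandScan guidance. It does not cover the takeover: the discordance rule needs the clinical assessment for more than blinding, and after a switch DAS determines the treatment.

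The planned sensitivity analyses on specialist time and visit numbers act on the relevant quantities and soften the point. Without stated ranges they cannot be dismissed, but none is described as charging for the safeguard or costing both arms alike. The claim in the Discussion is also comparative: it promises fewer assumptions than the earlier model, not none.

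A reader might infer more than the protocol supports:
- That rheumatologist cost is removed from the HandScan arm. It is reduced, since it is kept whenever a rheumatologist would have been required, and monthly escalation makes that likely at many early visits.
- That the mismatch can only favour HandScan. The schedule names no arm, and one reading allows the opposite sign.
- That switched patients are certainly costed by the HandScan rule. The article does not say, and a condensed article may leave this to the full economic plan.
- That the quoted correlation of 0.42 implies a particular switch rate. It relates the HandScan score to DAS28 in an earlier study, not to agreement of monthly remission decisions.
- That a rheumatologist performs every DAS44. The article does not say who does.

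**Conclusion.** The concern holds in this form: the base case combines the effects of HandScan plus a DAS safeguard with the specialist cost of HandScan alone, and no listed analysis clearly charges for the safeguard. On a common 10-visit schedule the rule by itself is worth 10 × (1 − q) charged visits per HandScan patient, or 7.5 to 2.5 for q between 0.25 and 0.75. Both q and the coverage of the schedule are assumptions, and unit costs are not given, so no monetary size can be stated. How much of the saving belongs to patients under DAS guidance depends on the switch share and on costing by randomized arm, neither of which the article fixes. The description as an evaluation from actual data is too strong, because specialist attendance and visit frequency are both assumed. This affects a secondary outcome that is also a declared aim. It merits correction but has no bearing on the primary HAQ analysis.

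**What to change.** 1. Keep the conditional rheumatologist charge for HandScan-arm visits while HandScan guides treatment.
2. Cost every HandScan-arm visit after a switch exactly as a DAS-arm visit.
3. State that the assumed visit schedule applies to both arms.
4. Add a labelled scenario that charges the HandScan arm for the clinical assessment the discordance rule needs and costs both arms by one rule.
5. Describe the evaluation as partly model-based, naming specialist attendance and visit frequency as the assumed components.

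The cost is a few sentences in the economic plan and slightly more analysis. The software already tracks discordances and implements the switches, so no new data collection is needed. The cost result may turn out less favourable to HandScan.

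### The QALY comparison names no adjustment for baseline EQ5D utility; read as written, it gives up precision and can mislead if the arms differ by chance at baseline

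*Protocol article*

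**What the plan says.** The Secondary outcomes section sets out the economic evaluation in some detail: three perspectives, discount rates, multiple imputation, cost-effectiveness planes and acceptability curves. The estimator is given in one phrase: differences in QALYs and costs "will be calculated using bootstrapping (5000 resamplings, with replacement". QALYs are defined as "life years multiplied by the utility value, as calculated using EQ5D". No covariate is named. Baseline utility is also absent from the listed variations: "Sensitivity analyses will be performed for time spent by rheumatologists, number of visits, QALYs (according to either EQ5D or SF36), costing method", followed by discount rates.

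The baseline value is available: "Quality of life will be evaluated at baseline and after 3, 6, 12, and 18 months using SF36 and EQ5D questionnaires". The Assessments section gives the same schedule.

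The HAQ analysis is specified differently. Under Primary outcome analyses it is a linear model "controlling for baseline HAQ, center (stratification factor in the randomization), and the baseline covariates age, gender, disease activity (DAS28), rheumatoid factor, and anti-CCP", and the longitudinal HAQ model uses the same covariates. The Discussion reports of the earlier economic model: "Implementation of the HandScan as a monitoring tool was modeled at comparable costs and comparable effects as using clinical assessments". The trial-based evaluation is meant to validate that result.

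**The concern.** A patient's 18-month QALY depends on baseline utility in two ways. If QALYs are computed as an area under the utility curve, the baseline value is part of the sum. Baseline utility also predicts the later utilities that make up the rest. If one arm happens to start with better utility, a plain difference in mean QALYs carries that head start along with any effect of the guidance method.

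This deserves attention here because the earlier model found comparable effects, so the QALY difference is expected to lie near zero. A modest chance component can then move the point noticeably along the effect axis of the cost-effectiveness plane. An avoidably wide interval also makes the acceptability curve less informative. The authors adjust HAQ for its own baseline, and the same step is open to them for QALYs.

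**Working it through.** **Number per arm.** The Sample size section gives SD 0.4, margin 0.2, one-sided 0.05 and 80% power.
- Normal approximation: n = 2 × 0.4² × (1.645 + 0.842)² / 0.2² = 49.5, so 50 per arm. The *t*-based calculation gives 51 (power 80.6%), which is the article's figure.
- Dropout: 102 × 1.1 = 112.2. The article says: "Taking into account 10% drop-out, total sample size was set at 112 patients". At 1:1 this is 56 per arm.
- The Abstract says 61 per arm. That conflict needs reconciling separately; it hardly matters here, as shown below.

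**Assumed inputs.** The article gives no EQ5D SD, slope or correlation. Assumed ranges: utility SD 0.15 to 0.25; slope of later on baseline utility 0.4 to 0.6; baseline-QALY correlation r of 0.5 to 0.6.

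**Chance imbalance at baseline.** SE = SD × √(2/56).
- SD 0.15: 0.028; SD 0.20: 0.038; SD 0.25: 0.047.
- At SD 0.20 the 95% limits are ±1.96 × 0.0378 = ±0.074. With 61 per arm they would be ±0.071.

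**Carry-over into the QALY difference.** Simple form: SE × slope × 1.5 years.
- Low end: 0.0283 × 0.4 × 1.5 = 0.017. High end: 0.0472 × 0.6 × 1.5 = 0.043.
- With trapezoid weights at 0, 3, 6, 12 and 18 months (0.125, 0.25, 0.375, 0.5 and 0.25 years; an assumption about the QALY formula), the multiplier is 0.125 + 1.375 × slope, or 0.675 to 0.95. The range becomes 0.019 to 0.045.
- The direct part is small: 0.125 × 0.074 = 0.009 QALY. Most of the effect comes through correlation with later utilities.

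**Precision.** SE ratio, adjusted to unadjusted = √(1 − r²).
- r = 0.5: √0.75 = 0.87, so 13% smaller. r = 0.6: √0.64 = 0.80, so 20% smaller.
- Stated the other way, the unadjusted SE is 15% to 25% larger than the adjusted one (1/0.866 and 1/0.80).
- In patients: 1/(1 − r²) = 1.33 to 1.56, so the gain is worth 33% to 56% more patients for this comparison.

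**Simulation.** 8,000 trials, 56 per arm, utility SD 0.20, equal correlation ρ between all visits, no true effect, trapezoid QALYs.

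| ρ | SE unadjusted | SE adjusted | SE reduction | QALY shift per 0.01 baseline imbalance, unadjusted |
|---|---|---|---|---|
| 0.3 | 0.039 | 0.033 | 14% | 0.005 |
| 0.5 | 0.044 | 0.032 | 27% | 0.008 |
| 0.7 | 0.049 | 0.028 | 43% | 0.011 |

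- Both estimators average about zero, and the adjusted difference shifts by about zero with baseline imbalance.
- In this model r = (0.125 + 1.375ρ) / √(0.53125(1 − ρ) + 2.25ρ), which is 0.53, 0.69 and 0.83 for the three rows. The assumed r of 0.5 to 0.6 therefore sits near the first row.
- An imbalance of 0.074, at the edge of the 95% limits, moves the unadjusted difference by 0.074 × 0.53 = 0.04 (ρ = 0.3) to 0.074 × 1.09 = 0.08 QALY (ρ = 0.7). That is about 1.0 to 1.6 of its own standard errors.

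**The case against.** The strongest reply is that the article never says the comparison is unadjusted. Bootstrapping is a way of resampling; it can be applied to a regression-adjusted difference as readily as to a difference in means. The Secondary outcomes section names covariates for none of its analyses, including the quality-of-life and radiographic models, so its silence does not single out QALYs. A condensed article may also leave such a specification to a fuller document. This stands in part: the plain difference is the natural reading of a detailed paragraph placed beside a HAQ section that lists its covariates, but it is an inference.

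The second reply concerns consequences, and it stands in full. Randomisation makes the plain difference unbiased on average, and the bootstrap spread, hence the plane and the acceptability curve, already contains the chance imbalance. A reader might infer that the cost-effectiveness result would be driven mainly by baseline imbalance. That is not supported: r of 0.5 to 0.6 means baseline utility accounts for 25% to 36% of the variance of the QALY difference, and more than half is reached only in the ρ = 0.7 setting of the simulation. Nor is any effect of baseline utility on the cost axis shown. Centre adjustment has little imbalance to correct, because the randomisation lists are per centre in blocks of four.

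**Conclusion.** The point holds as a loss of precision and as exposure to error in the particular trial that is run, not as bias. Under the assumed correlation of 0.5 to 0.6, adjusting for baseline utility makes the standard error of the QALY difference 13% to 20% smaller. Under the assumed SD and slope ranges, it removes a chance component with standard error of about 0.017 to 0.043 QALY. All of these inputs are assumptions, and the gain would be larger if utilities correlate more strongly between visits.

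It would go too far to conclude that the authors decided against adjustment, or that the planned interval would be invalid; the text supports neither. This is a worthwhile improvement to an analysis that the article leaves open, not an error in it.

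**What to change.** State whether the bootstrapped QALY difference is adjusted. If it is not, then in each resample, drawn within arm and keeping each patient's costs and QALYs together, regress QALYs on arm, baseline EQ5D utility and centre. Use the adjusted difference for the cost-effectiveness plane and the acceptability curves. Report the unadjusted difference as a further sensitivity analysis. Adjusting costs for centre is optional, with a small expected gain.

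The change takes a few lines of code and no new data, since baseline EQ5D and centre are already recorded. It should be written down before the outcome data are compared by arm.
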